## Abstract

**Background:**

Although endovascular recanalization therapy demonstrates robust clinical efficacy in acute ischemic stroke (AIS), not all victims of these cerebrovascular accidents can benefit from it and achieve a favorable prognosis after successful reperfusion. Therefore, alternative neuroprotective strategies are urgently needed for AIS patients after vessel recanalization. Nitric oxide (NO) levels are low after AIS and NO donor drugs may be neuroprotective against cerebral ischemia–reperfusion injury. Glyceryl trinitrate (GTN), often used in the clinic as a NO donor, may provide a novel neuroprotective strategy. This rationale, design, and protocol for a prospective pilot study plans to explore the preliminary safety, feasibility, and neuroprotective benefits of Arterial Glyceryl Trinitrate in Acute Ischemic Stroke after Thrombectomy for Neuroprotection (AGAIN).

**Methods:**

AGAIN, a prospective RCT, is proposed for AIS patients after mechanical thrombectomy. Subjects will be randomly assigned in a 1:1 fashion (*n* = 40) to either the control group or the intervention group. Participants assigned to the intervention group will be administered 800 μg GTN in the catheter immediately after recanalization, whereas those in the control group will be administered the same volume of normal saline. All participants from either group will be given concurrent treatment with standard of care therapies in accordance with the current guidelines for stroke management. The primary outcome is safety [symptomatic intracranial hemorrhage (ICH), hypotension, neurological deterioration, ICH, fatal ICH, as well as headache, tachycardia, emesis, and seizures], whereas secondary outcomes included changes in poststroke functional outcomes, infarction volumes, and blood nitrate index detection.

**Discussions:**

This study is a prospective randomized controlled trial to test the safety and efficacy of intra-arterial GTN in AIS patients after endovascular therapy. The results from this study will give insight for future GTN studies and new neuroprotective strategies for future AIS treatment strategies.

**Trial registration number:**

ChiCTR2100045254. Registered on March 21, 2021.

## Background

Acute ischemic stroke (AIS) is a severe disease and devastating public health concern– it carries a substantial socioeconomic burden with remarkably high morbidity and mortality rates [1, 2]. New medical advances, including the new generation of stent-retrievers, have been successful in improving the rates of revascularization after AIS and in expanding the temporal intervention window for patients who suffer large vessel occlusions (LVO). Advances such as these have lowered rates of disability and mortality and improved post-stroke outcomes. However, despite this cutting-edge technology, there is an apparent discrepancy between the use of effective recanalization and the ability to regain pre-stroke functional abilities. Indeed, not only does the mortality rate remain at 15.3%, but only 46% of individuals with anterior circulation AIS who are treated with endovascular therapy achieve functional independence after 90 days [3]. Furthermore, there is significant heterogeneity across studies reporting the long-term outcomes of thrombectomy and several aspects of this technique are yet to be optimized, such as the time window for effective treatment [3–6]. As a result of these uncertainties, attention must be given not only to advances in vascular recanalization, but also to neuroprotection in the post-stroke setting in order to maximize the potential of these emerging therapies. Exploring fast and effective neuroprotection strategies to supplement mechanical thrombectomy will become a key strategy for improving the prognosis of the post-stroke patient [7]. We hypothesized that glyceryl trinitrate (GTN), a donor of nitric oxide (NO), may benefit patients in the context of AIS after endovascular recanalization.

The efficacy of reperfusion after ischemic stroke is limited by post-ischemic inflammatory changes, including reactive oxygen species (ROS) formation and accumulation, which may cause apoptosis as well as unregulated and pathologic cell death [8]. ROS and nitrogen species are highly destructive products of ischemic-reperfusion injury and that can exacerbate neuronal death through DNA damage, lipid peroxidation, and protein oxidation [9]. NO plays a pivotal part in hypoxic signaling and, at physiologic and therapeutic levels, exerts powerful cytoprotective effects after ischemia and reperfusion in a variety of tissues, including neurologic tissue [10, 11]. Though the mechanism remains elusive, various studies have reliably exhibited reduced cytoprotection when subjects were administered NO scavengers or in experiments where NO synthase was knocked out or inhibited [12–14]. ROS formation induced by reperfusion contributes to a decrease in the bioavailability of NO, thus limiting its ability to promote various protective mechanisms after stroke, such as vasodilation, inflammation inhibition, and preservation of endothelial integrity under hypoxic conditions [15]. NO donors are a category of drugs, independently of its endogenous sources, whose common mechanism is a propensity to release NO or a NO-related substance in vitro or in vivo [16]. Abundant preclinical research suggests NO donors can safely decrease infarction volume, increase cerebral blood flow, and better functional outcomes in AIS in both transient and permanent stroke models [17]. Additionally, NO donors’ neuroprotective effect has been shown to alleviate ischemia–reperfusion injury at various levels in multiple different ways, including modifying cellular oxidative status, inhibiting activity of monocytes, and reducing primary hemostasis [18].

GTN is a vasodilator approved by the Food and Drug Administration which acts as an NO donor and has been experimented with for neuroprotection in AIS. Transdermal GTN has been shown to lower blood pressure without any deleterious effects on platelet function or changes to the middle cerebral artery (MCA) blood flow velocity or to regional cerebral blood flow in patients suffering an AIS [19–22]. A recent RCT with a larger sample size studied the efficacy of transdermal GTN in high blood pressure management in AIS (ENOS) similarly showed the GTN’s ability to lower blood pressure, but did not indicate an improvement in functional outcome following AIS [23]. However, NO donors’ neuroprotective effects following ischemic–reperfusion injury have consistently shown to be dependent on the dose, location, source and environment [24]. Considering these parameters and GTN’s short half-life, administering GTN as an arm or chest patch might not reach the cerebrovascular system in a way that enables it to confer significant or reliable benefits. Recently, arterial administration of GTN in MCAO animal models demonstrated a neuroprotective effect in AIS [24]. Rather, intra-catheter GTN administration might be a quicker, more effective method to allocate the full potential of GTN. To our knowledge, there is a paucity of literature regarding GTN’S efficacy and safety as an adjunctive method of neuroprotection to endovascular recanalization in AIS. Thus, this single-center, prospective randomized controlled study serves to assess the safety, feasibility, and preliminary efficacy of intra-catheter GTN administration post-mechanical thrombectomy.

## Methods/design

This study was registered on www.chictr.org.cn in April 2021 (ID: ChiCTR2100045254) and approved by the ethics committee of Luhe Hospital, Capital Medical University, Beijing, China.

### Study design

AGAIN is a prospective, randomized, controlled, single-center study designed to evaluate the safety and efficacy of GTN administration after mechanical thrombectomy in patients suffering an AIS within 6 h of symptom onset.

### Participants and screening

Eligible patients will be enrolled consecutively after undergoing endovascular therapy for AIS in the Beijing Luhe Hospital Stroke Center, Capital Medical University. Participants for this study will be recruited from the stroke center (the Stroke Intervention & Translational Center, SITC) in Beijing Luhe Hospital. Informed consent, which includes an explanation of potential benefits and risks, will be obtained from each participant. Once all participants have read the participant information sheet and provided written informed participation consent, they will be evaluated against eligibility criteria and, if eligible, will be enrolled in our study. Consent will be obtained by an appointed legal representative should the participant lack decision-making capacity, see Fig. 1.

**Fig. 1 Fig1:**
[figure not shown]
Flowchart of the study

*The inclusion criteria include*: 1) AIS patients with anterior circulation LVO who received endovascular therapy, 2) age between 18 and 80 years, 3) within 6 h from symptom onset to puncture, 5) baseline ASPECT score 6–10, 6) baseline NIHSS score 6–25.

*Exclusion criteria are as follows*: 1) lack of vessel recanalization (TICI score = 0), 2) evidence suggesting spontaneous vessel recanalization, 3) rapid spontaneous amelioration of neurological function to an NIHSS < 6 after vessel recanalization, 4) systolic blood pressure < 120 mmHg before GTN administration, 5) blood glucose < 2.7 or > 22.2 mmol/L, 6) evidence of coagulation disorders in laboratory studies, 7) pregnancy, 8) pre-stroke modified Rankin Scale (mRS) > 2, 9) no informed consent was obtained, 10) enrollment in other clinical studies within 3 months.

A physician unaffiliated with the study will monitor the safety and health status of participants. A safety quality control conference was held by the GCP committee twice a year and on an as needed basis. The safety of subjects was continuously monitored by Luhe Hospital Ethics Committee.

### Randomization and blindness

The participants will provide consent and assigned randomly in a 1:1 (*n* = 40) fashion to the two treatment groups with the use of computer-generated randomization. Interventionalists, outcome assessors, and investigators involved in data collection and analysis for the trial will be blinded to this assignment with the use of opaque envelopes.

### Interventions

Stroke patients that satisfy inclusion criteria will be assigned randomly to either the control group or experimental group. All patients will also receive standard stroke treatment, including antiplatelet or anticoagulation medications, antihypertensive medications, hyperlipidemia and hyperglycemia control, and neurotrophic treatment. In experimental group, 800 μg NTG will be diluted using 10 cc isotonic NaCl solution administered via catheter over 10 min after vessel recanalization. The control group will receive 10 cc isotonic NaCl administered via the catheter over 10 min.

### Outcomes and assessment procedures

Participant demographic information, stroke risk factors, occlusion site, and procedure of mechanical thrombectomy will be recorded. On hospital admission, ASPECTS (Alberta Stroke Program Early CT Score) and NIHSS (National Institute of Health stroke scale) scores will be determined and recorded for further analysis. Magnetic resonance imaging (MRI) or computerized tomography (CT) will be completed 24 h after mechanical thrombectomy. NIHSS and mRS scores will also be determined at baseline and at 24 h, day 7, 14, and 90 after stroke onset.

*Primary Outcomes (Safety Assessment)*. The primary safety consideration of AGAIN is the risk of symptomatic intracranial hemorrhage (ICH). The secondary safety outcomes include: 1) episodes of hypotension requiring clinical treatment during GTN administration; 2) neurological deterioration is defined as NIHSS score increasing more than 4 point from baseline to day 7; 3) ICH, fatal ICH; 4) death regardless of cause during the study period; 5) headache, tachycardia, emesis, and seizures.

*Secondary Outcomes (Efficacy Assessment)*. The main parameter to assess efficacy of AGAIN is functional independence on day 90 post-intervention (as determined by scores between 0 to 2 on the mRS scale, which are representative of functional independence), infarct volumes, NIHSS scores, and blood nitrate index detection [cyclic guanosine monophosphate (cGMP), L-arginine, and L-citrulline)]. The infarct volume is measured using the Siemens Syngo with Diffusion-Weighted Imaging (DWI) by the image tool (ROI) (this is done by outlining the infarcted area on each section in order to calculate the area and subsequently by multiplying this value from each layer by its respective thickness).

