### Estimation of sample size

Intra-catheter administration of GTN in AIS patients after mechanical thrombectomy is our first attempt to address the effect of GTN in AIS patients with endovascular therapy. There is no data available for reference. AGAIN is a pilot study to examine the study design, methods, procedures, inclusion criteria, and operational strategies. The results will be used to estimate the sample size and conduct a power analysis for a phase-2 trial. Based on two other protocols published in Frontiers in Neurology [25, 26], 10 to 20 participants per group may be adequate to assess the initial safety and feasibility trends of intra-catheter administration of GTN. Therefore, a similar number of sample of total 40 patients was selected in this pilot study.

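### Hypotension is counted only when it was treated, with no pressure criterion and no measured pressure among the outcomes, so the outcome is insensitive to the blood pressure effect the article itself expects

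*Protocol article*

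**What the plan says.** Under Outcomes and assessment procedures, the first secondary safety outcome is "episodes of hypotension requiring clinical treatment during GTN administration". That section gives no pressure value, no size of fall and no criterion for when treatment is required. It names no measured blood pressure among the recorded data, the safety outcomes or the efficacy outcomes.

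The abstract (Methods) describes the item differently. Its primary safety list reads "symptomatic intracranial hemorrhage (ICH), hypotension, neurological deterioration, ICH, fatal ICH" and continues with other events. Hypotension stands there without any treatment condition.

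Other places that bear on the point:
- **Background:** "Transdermal GTN has been shown to lower blood pressure".
- **Exclusion criteria (Participants and screening):** "systolic blood pressure < 120 mmHg before GTN administration". This is the only blood pressure figure in the article. It governs entry and is not an outcome.
- **Interventions:** the active drug is "administered via catheter over 10 min after vessel recanalization"; the control arm receives saline over the same length of time.
- **Randomization and blindness:** "Interventionalists, outcome assessors, and investigators involved in data collection and analysis for the trial will be blinded to this assignment".
- **Estimation of sample size:** "a similar number of sample of total 40 patients was selected in this pilot study", on the ground that "10 to 20 participants per group may be adequate to assess the initial safety and feasibility trends".
- **Statistical analyses:** the team goes on to a phase-2 trial if the arms show no difference in how often adverse events occur or in functional outcome at 90 days. Categorical outcomes are tested by χ² or Fisher's exact test at 0.05.

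**The concern.** Treatment is a condition of counting. The outcome therefore records a decision to treat, not the pressure reached. Two patients with the same fall can be classified differently, and a large fall that was only observed does not count.

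That is a weak choice for this drug. The article expects GTN to lower pressure and screens on systolic pressure before dosing. The pilot is also meant to supply the inputs for sizing the next trial. A treated-event count gives neither the mean fall nor its SD.

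The safety comparison feeds the phase-2 step. The smaller the share of falls that are treated, the easier it is to find no difference in hypotension, whatever GTN does to pressure.

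**Working it through.** **Inputs from the article.** The total is 40, allocated 1:1. The upper end of the quoted range, 20 per group, gives 2 × 20 = 40, so the stated sample size reproduces. It rests on precedent; no power, rate or effect size is given. The test is Fisher's exact, two-sided at 0.05.

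**Assumptions.** The article gives no rate of hypotension and no difference or SD for blood pressure. All such values below are assumed and shown over a range.

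**Step 1: what the event comparison can show with 20 per arm.** For x events v 0, the two-sided Fisher p is 2 × C(20,x)/C(40,x).
- 4 v 0: 2 × 4,845/91,390 = 0.106.
- 5 v 0: 2 × 15,504/658,008 = 0.047.

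Five treated episodes against none is thus the smallest such result that reaches significance. If 0 of 20 are observed, the two-sided 95% upper limit is still 1 − 0.025^(1/20) = 16.8%.

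**Step 2: effect of the treatment condition.** Assume true falls in 40% v 10%, and that the same share s of falls is treated in both arms. The counted rates are then 0.40s and 0.10s. Power is the sum of the binomial probabilities of all tables with Fisher p < 0.05.

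| Share treated | Counted rates | Power |
|---|---|---|
| 100% | 40% v 10% | 49% |
| 75% | 30% v 7.5% | 33% |
| 50% | 20% v 5% | 17% |
| 25% | 10% v 2.5% | 3% |

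The pressure effect is the same in every row. Only the readiness to treat changes.

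**Step 3: what a measured pressure would give.** The standard error of the difference is SD × √(2/20) = 0.316 × SD. With 38 degrees of freedom t = 2.024, so the 95% CI half-width is 2.024 × 0.316 × SD:
- SD 15: 9.6 mmHg
- SD 20: 12.8 mmHg
- SD 25: 16.0 mmHg

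Two-sided t-test power comes from the noncentral t with noncentrality difference/(0.316 × SD).

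| True difference | SD 15 | SD 20 | SD 25 |
|---|---|---|---|
| 10 mmHg | 54% | 34% | 23% |
| 15 mmHg | 87% | 64% | 46% |
| 20 mmHg | 98% | 87% | 69% |

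**Reading the two tables together.** Nothing links a 40% v 10% rate of falls to a given difference in mmHg, so the tables do not show that one endpoint beats the other by a fixed amount. Step 2 shows how much power the treatment condition can cost. Step 3 shows that a measured pressure yields an estimate with a known margin that does not depend on how many falls are classed as events.

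**The case against.** The strongest case on the other side is that hypotension needing treatment is the clinically meaningful harm, and that a lower reading alone is a drug effect. The Background reports lower pressure on transdermal GTN without harm to platelet function or cerebral flow. A severity-based event is a coherent choice for a 40-patient pilot, and an article may leave monitoring schedules and form fields to the full protocol. This stands as far as it goes: treated hypotension should stay, and the absence of a monitoring schedule is no finding. The point rests on the definition that the article does state, and on its mismatch with the abstract.

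A reader might infer more than the document supports in five ways.
- **That pressures are not recorded, or are thrown away.** The article does not say so. The full protocol may record them, and the safety list is introduced as inclusive. Untreated falls are outside this outcome as written; they may still be captured elsewhere, for example as adverse events.
- **That operator discretion biases the comparison.** Operators and assessors are stated to be blinded, and this is a single-center trial. Unless a visible pressure drop reveals the arm, the consequence is under-counting and lost sensitivity.
- **That the outcome is strictly yes/no.** The text speaks of episodes, which could be counted. A count would still be conditional on treatment.
- **That measured pressure is always the more powerful endpoint.** It is not: a 10 mmHg difference has only 34% power at SD 20 and 23% at SD 25, against 49% for 40% v 10% with every fall counted.
- **That adding a pressure outcome would by itself change the phase-2 decision.** The rule refers to the incidence of adverse events and to functional outcome. A mean pressure is neither, so it enters only if the plan says so.

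**Conclusion.** The point holds as a limited one about the outcome definition. Hypotension counts only if treated, no pressure criterion is given, no measured pressure is named as an outcome, and the abstract and the outcomes section disagree on the treatment condition. The outcome is therefore insensitive to the pressure effect that the article expects.

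The size depends on an unknown, the share of falls that are treated. Under assumed true rates of 40% v 10% and an equal share in both arms, power drops from 49% to as little as 3%. If larger falls on GTN were treated more readily, the equal-share assumption would overstate the loss. A measured systolic difference would be known to within about 10 to 16 mmHg for SDs of 15 to 25. That is useful for planning the next trial even where the test is not significant.

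Reading no difference at 20 per arm as reassurance is a wider weakness that affects every safety outcome. It is not specific to hypotension.

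**What to change.** 1. Reconcile the abstract and the outcomes section so that hypotension has one stated definition and one place in the outcome hierarchy.
2. Keep treated hypotension as a safety outcome.
3. Add the lowest systolic pressure, and the fall from the pre-infusion reading, as safety outcomes. Take them from the monitoring record over the same interval in both arms. The present wording ties the window to the GTN infusion, which has no literal counterpart under saline.
4. Report the between-arm mean difference with its 95% CI, and state that it will be considered alongside adverse-event incidence in the decision on a phase-2 trial.

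The cost is a few case-report-form fields and one more comparison, assuming that pressure is already monitored during the procedure. No clinical threshold or treatment rule is proposed.

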### Estimation of sample size

Intra-catheter administration of GTN in AIS patients after mechanical thrombectomy is our first attempt to address the effect of GTN in AIS patients with endovascular therapy. There is no data available for reference. AGAIN is a pilot study to examine the study design, methods, procedures, inclusion criteria, and operational strategies. The results will be used to estimate the sample size and conduct a power analysis for a phase-2 trial. Based on two other protocols published in Frontiers in Neurology [25, 26], 10 to 20 participants per group may be adequate to assess the initial safety and feasibility trends of intra-catheter administration of GTN. Therefore, a similar number of sample of total 40 patients was selected in this pilot study.

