### Statistical analyses

The endpoint event in the present study will be assessed using the concept of intention-to-treat (ITT). In the event that no differences in incidence of adverse events or functional outcomes are found at 90 days when comparing the experimental and control groups, our team will proceed onto a phase-2 trial.

The Kolmogorov–Smirnov test for normality and the equal variance will be conducted prior to any other statistical analysis methods. For continuous variables with normal distribution, a 2-sided *t* test for independent samples will be applied in order to detect differences between the groups. A Mann–Whitney U test will be performed for continuous variables that have a non-normal distribution. For categorical variables, χ2 or Fisher exact tests will be used when fitting. A *p* value of < 0.05 will be the threshold to determine statistical significance. Statistical analysis will be performed on SPSS 22.0.

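### The sample-size section does not say what 20 patients per arm can show for symptomatic ICH, and the planned significance test says little about safety at that size; an exact interval would be a cheap improvement

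*Protocol article*

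**What the plan says.** **Size.** The section Estimation of sample size says of earlier experience with this use of GTN: "There is no data available for reference". It describes AGAIN as a pilot whose results will be used to size a phase-2 trial. The number comes from precedent: "Based on two other protocols published in Frontiers in Neurology [25, 26"], it states that "10 to 20 participants per group may be adequate to assess the initial safety and feasibility trends of intra-catheter administration of GTN", and concludes that "a similar number of sample of total 40 patients was selected in this pilot study". The section Randomization and blindness has patients "assigned randomly in a 1:1" ratio, hence 20 per arm.

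**Outcome.** The section Outcomes and assessment procedures says: "The primary safety consideration of AGAIN is the risk of symptomatic intracranial hemorrhage (ICH").

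**Analysis.** The section Statistical analyses names chi-square or Fisher exact tests for categorical variables and adds: "A *p* value of < 0.05 will be the threshold to determine statistical significance". It names no interval for the symptomatic ICH rate or for the difference between arms.

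**Limitation.** The Discussion acknowledges a single center and a small sample. It does not say which symptomatic ICH risk the trial could or could not exclude.

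**The concern.** The sample-size section speaks of adequacy for initial safety but attaches no quantity to it: no expected rate, no tolerable rate and no precision. Having no earlier GTN data does not prevent this, because the precision of a zero or low count depends only on the number of patients.

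The stated analysis does not fill the gap. With 20 per arm and an uncommon event, a test at p < 0.05 will usually be non-significant whether or not GTN raises the risk. A reader who sees a size described as possibly adequate for safety, followed by a non-significant comparison, may take the result as reassurance. At stake is how the primary safety result is read and carried into phase-2 planning. The point does not depend on the article's rule for going on to phase 2.

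**Working it through.** **Inputs from the article.** Total 40, allocation 1:1, so n = 40 / 2 = 20 per arm. The primary safety event, symptomatic ICH, is binary. The threshold is 0.05, so two-sided 95% limits are the matching choice. The article gives no event rate, effect, power or precision target, so 40 cannot be re-derived; only 2 × 20 = 40 can be checked, and it agrees.

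**1. What a low count in the GTN arm excludes.** These are exact (Clopper-Pearson) two-sided 95% upper limits.

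- 0/20: 1 − 0.025^(1/20) = 0.168, or 16.8%.
- 1/20: the p that solves (1 − p)^20 + 20p(1 − p)^19 = 0.025 is 0.249, or 24.9%.
- 2/20: by the same method, 31.7%.

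The type of interval changes little for 0/20:

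| Method | Upper limit, 0/20 |
|---|---|
| Exact, two-sided 95% | 16.8% |
| Wilson, 1.96² / (20 + 1.96²) | 16.1% |
| Rule of three, 3/20 | 15.0% |
| Exact, one-sided 95%, 1 − 0.05^(1/20) | 13.9% |

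**2. What the planned test can detect.** If one arm has no events, the two-sided Fisher p-value for x events in the other is 2 × C(20, x) / C(40, x).

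- x = 4: 2 × 4,845 / 91,390 = 0.106, not significant.
- x = 5: 2 × 15,504 / 658,008 = 0.047, significant.

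So with no event in one arm, the other needs at least 5 of 20 (25%). The expected number of events per arm in these tables is 2 to 2.5, so Fisher's test is the fitting one of the two named.

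**3. Power of that test under assumed rates.** The rates below are illustrations and are not in the article.

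| Control rate | GTN rate | Exact power, Fisher, 20 per arm |
|---|---|---|
| 5% | 10% | 1.7% |
| 5% | 15% | 7.0% |
| 5% | 20% | 16.8% |

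The 16.8% in the last row is a power and only by coincidence equals the 0/20 limit.

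**4. Chance of seeing no event in the GTN arm,** (1 − p)^20, again at assumed rates: 0.95^20 = 36% if the true rate is 5%, and 0.90^20 = 12% if it is 10%.

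**The case against.** The strongest reply is that the article states nothing false. It says the size may be adequate, and only for initial safety and feasibility trends. It calls the study a pilot, and the Discussion admits that the sample is small. Sizing a pilot by precedent is common. The choice of interval is often left to a statistical analysis plan, which is not shown here. Most of this stands, and it is why the point is an improvement and not an error.

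Three stronger readings should be resisted.

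- A reader might infer that the article claims 20 per arm is enough to establish safety, and that the calculation refutes this. The hedged sentence makes no such claim. The article also gives no expected or unacceptable symptomatic ICH rate against which 16.8% could be called too high.
- A reader might apply the calculation to 10 per group, where the limits are much wider. That is only the low end of the range the article quotes; the planned arm is 20.
- A reader might turn to the Background, which reports that "only 46% of individuals with anterior circulation AIS who are treated with endovascular therapy achieve functional independence after 90 days" and gives a mortality of 15.3%. Neither is a symptomatic ICH rate, so neither shows what the trial can say about its primary safety outcome.

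What survives is narrower. The Discussion admits the small size but never translates it into a risk that could be excluded. The article does state its method for categorical outcomes, and that method is a poor vehicle for a rare safety event at 20 per arm.

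**Conclusion.** The point holds as a cheap improvement to the wording and to the reported analysis. It gives no ground for changing the sample size. With 20 per arm, 0 or 1 symptomatic ICH in the GTN arm would exclude only true rates above 16.8% or 24.9% respectively. The planned Fisher test would stay non-significant even at 4 events against 0.

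These figures rest only on n = 20 per arm with full follow-up for the event, and on two-sided exact limits. A one-sided 95% limit for 0/20 would be 13.9%, which does not alter the conclusion. The power figures and the chances of seeing no event rest on assumed rates and serve as illustration. Whether a limit near 17% is acceptable for a pilot is a clinical judgement that the article does not supply and this review does not make.

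**What to change.** Keep 40 patients.

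1. In Estimation of sample size, replace the adequacy sentence with wording such as: *The size is pragmatic. With 20 patients per arm, no symptomatic ICH in the GTN arm would exclude a true rate above 16.8%, and one event a rate above 24.9% (two-sided exact 95% limits). Smaller risks cannot be excluded.*
2. In Statistical analyses, make the exact 95% confidence interval for the GTN-arm rate, together with a confidence interval for the risk difference, the reported result for symptomatic ICH. The method for the difference should cope with zero cells: a simple Wald interval has zero width at 0 versus 0, whereas a Newcombe interval built from Wilson limits gives ±16.1 points. A Fisher p-value may stand beside these.
3. State that the safety conclusion is limited to what those intervals exclude, and that a non-significant test will not be read as evidence of safety.

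The cost is a few sentences and two interval calculations, with no extra patients or data. The downside is that the stated adequacy will look less favourable.
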